**Interviews (clinician-rated)**							
Comorbid disorders, severity, chronicity; remission	SCID-5	X			X		
Depression response	QIDS	X			X		
Anxiety response	HAM-A	X			X		
Serious adverse events	Checklist				X		

*T0, Baseline; T1, 6 weeks; T2, 12 weeks; T3, 18 weeks post inclusion; T4, 24 weeks post inclusion; T5, 12 months post inclusion follow-up; PHQ-ADS, Patient Health Questionnaire Anxiety and Depression Scale; AQOL, Assessment of Quality of Life; ZUF-8, Questionnaire for Patient Satisfaction-8; WAI-SR, Working Alliance Inventory—Short Revised; TIC-P, Trimbos Institute and Institute of Medical Technology Questionnaire for Costs Associated with Psychiatric Illness; SR, Self-Report Assessment; CTS, Childhood Trauma Screener; F-SozU K-6, Perceived Social Support Questionnaire brief form; NEQ, Negative Effects Questionnaire; C-SSRS, Columbia-Suicide Severity Rating Scale; LPFS-BF 2.0, Level of Personality Functioning Scale Brief Form 2.0; SMST, Self-Management Self-Test; MHSES, Mental Health Self Efficacy Scale; TAI, Therapeutic Agency Inventory; CBTSQ, Cognitive-Behavioral Therapy Skills Questionnaire; UCLA, UCLA Three-Item Loneliness Scale; CEQ, Credibility-Expectancy-Questionnaire; APOI, Attitudes toward Psychological Online Interventions; FRAPT, Fragebogen zur Messung persönlicher Therapieziele [Questionnaire for measuring personal therapy goals]; SCID-5, Structured Clinical Interview for DSM-5; QIDS, Quick Inventory of depressive Symptomatology; HAM-A, Hamilton Anxiety Rating Scale*.

**Table 4 T4:** Overview of the assessments (therapists).

**Variable**	**Instrument**	**Time of measurement**					
		**T0**	**T1**	**T2**	**T3**	**T4**	**T5**
Working alliance	WAI-SR-T				X		
Sociodemographics	SR	X					
Attitudes toward blended therapy	APOI	X			X^*^		
Attitudes toward evidence-based practice	EBPAS-D36	X					
Willingness to use digital health interventions	SR	X					
Barriers/facilitators in the use of digital health interventions	SR	X					
Acceptance of components of blended therapy	SR	X					
Determinants of behavioral change	TDF				X^*^		
Degree of normalization	NoMAD				X^*^		

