#### Side Effects and Adverse Events

We include different ways of monitoring and assessing side effects and (serious) adverse events [(S)AEs] adapted from the National Institute for Health Research recommendations (88) and Horigian et al. (89) who give general principles to define (S)AEs.

We define AEs as adverse or unintended symptoms or conditions that are inconsistent in nature or severity with the present information about the effects of the intervention. SAEs include the following events: (1) emergency hospitalization due to mental illness, (2) breakdown of a close, important relationship, (3) intoxication with a psychotropic substance requiring medical care, (4) self-injury (intentional) requiring medical care, (5) suicide or suicide attempt, (6) acute psychosis.

(S)AEs may be reported in telephone interviews and during psychotherapy sessions. Psychotherapists and interviewers are required to report (S)AEs to the trial evaluation administration. In addition, the possible occurrence of SAEs is systematically queried at the end of the telephone interview at T3.

Additionally, possible negative effects of the psychotherapies are assessed by means of the 20-item version of the Negative Effects Questionnaire [NEQ; 20 items; (90, 91)] which measures the frequency (score range: 0–20) and impact (score range: 0–80) of several different negative effects during the treatment period. Internal Consistency of the NEQ is reported to be α = 0.95 (90). Moreover, depression and anxiety symptom deterioration are determined by means of the QIDS-C and HAM-A.

Within the online-questionnaires suicidal and self-injurious thoughts and behaviors will be assessed by means of a modified version of the Columbia-Suicide Severity Rating Scale (92) at baseline (T0) and post-treatment (T3). At all times of measurement suicidal tendencies are measured by PHQ-ADS Item 9.

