##### Cost Measures

The health-economic evaluation will be based on claims data provided by the statutory health insurance companies AOK Baden-Wuerttemberg and Bosch BKK and the German version of the Dutch cost questionnaire Trimbos Institute and Institute of Medical Technology Questionnaire for Costs Associated with Psychiatric Illness [TiC-P; (94, 95)], which was specifically adapted to the population of psychotherapy outpatients in Germany. Claims data will contain basic information on the insured persons like sex, age, and profession as well as information on costs, diagnoses, and treatments for the following areas: in- and outpatient care, rehabilitation, prescribed medication, and therapeutic appliances and remedies, as well as sickness benefits and disability pension. Each online session will be charged with 20 €. In addition, Ulm University will provide information on costs for providing the digital treatment to psychotherapists. We will use the TiC-P for collecting data on patient and family costs (e.g., out-of-pocket expenses) and productivity costs due to presenteeism (i.e., reduced efficiency while at work). Lost workdays due to presenteeism will be computed by taking into account the number of work days for which the participant reported reduced functioning weighted by the reported corresponding inefficiency score for those days (96).

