#### Procedure on (S)AEs

Information about potential (S)AEs are obtained within diagnostic interviews, online questionnaires, and during therapy sessions. Whenever a (S)AE is detected, the incidence will be documented by either the therapist or the study personnel. During the treatment period especially the therapist is responsible for dealing with occurring (S)AEs and is informed by the study personnel about (S)AEs identified through answers of patients within the interviews or questionnaires. Critical answers within interviews are identified and documented by the interviewers who are trained in recognizing (S)AEs and provided with a detailed instruction in dealing with suicidality during interviews. Critical answers within questionnaires as defined by a score >1 on PHQ-ADS Item 9 will be forwarded to the therapist. Therapists will have to document (S)AEs and inform the study administration within 48 h on weekdays (SAEs) or within 1 week (AEs). Events occurring during the follow-up period are documented and handled by the study personnel by automatically sending information on help and emergency numbers and offering a meeting appointment via telephone for patients who give critical answers within the interviews or questionnaires. Critical answers as defined as a score >0 on PHQ-ADS Item 9 and selected items of our modified version of the Columbia-Suicide Severity Rating Scale will lead to automatic messages to patients with information on help and emergency numbers at all times of measurement. Documentations of (S)AEs will be forwarded to an independent Data Safety Monitoring Board (DSMB) which will monitor the frequency and severity of the occurring (S)AEs. Every 6 months the DSMB will be informed about documented (S)AEs and the recruitment process and if necessary can give recommendations for discontinuation or modification of the study.

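### After week 18 no scheduled patient assessment asks about the six defined serious adverse events, so they are not systematically ascertained for the last 34 of 52 weeks

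*Protocol article*

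**What the plan says.** The protocol article lists six SAEs under Side Effects and Adverse Events: emergency hospitalisation for mental illness, breakdown of a close relationship, intoxication needing medical care, intentional self-injury needing medical care, suicide or attempted suicide, and acute psychosis. Events may be reported in interviews or therapy sessions, and in addition "the possible occurrence of SAEs is systematically queried at the end of the telephone interview at T3". Table 3 gives the SAE checklist one mark, at T3.

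Procedure on (S)AEs makes the therapist chiefly responsible during the treatment period. For the time afterwards it says: "Events occurring during the follow-up period are documented and handled by the study personnel by automatically sending information on help and emergency numbers", together with the offer of a telephone appointment to patients whose answers in interviews or questionnaires are critical. It adds that a raised item 9 score and "selected items of our modified version of the Columbia-Suicide Severity Rating Scale will lead to automatic messages to patients", at every measurement time.

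The schedule runs past T3. The legend of Table 3 defines "T3, 18 weeks post inclusion" and "T5, 12 months post inclusion follow-up".

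**The concern.** Comparing the safety of both blended versions with standard CBT is one of the study aims in the Introduction. Depression and anxiety are followed for 12 months in all arms, but patients are asked directly about SAEs only up to week 18. After that, whether an SAE is recorded depends on the patient volunteering it or on a therapist learning of it and reporting it. Such a record is hard to compare between arms. Therapists are not blinded, and planned on-site contact during the trial sessions differs: at most 8 standard sessions in fix, a number chosen by the therapist in flex, and up to 16 in CBT. After the trial sessions, contact depends on who remains in therapy, which the allocated treatment may itself influence. The DSMB receives documented events, so a low late count could reflect limited ascertainment as well as a low rate.

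**Working it through.** There is no stated figure to reproduce. The check sets the schedule beside the safety text.

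**Scheduled safety sources** (Table 3; Side Effects and Adverse Events)

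| Source | T0 | T1 | T2 | T3 | T4 | T5 |
|---|---|---|---|---|---|---|
| SAE checklist | | | | X | | |
| Interviews (SCID-5, QIDS, HAM-A) | X | | | X | | |
| C-SSRS | X | | | X | | |
| NEQ | | | | X | | |
| PHQ-ADS item 9 | X | X | X | X | X | X |

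Apart from PHQ-ADS, T4 holds AQoL, TiC-P and medication, and T5 holds medication. As the article describes them, none of these asks about the six SAEs.

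**Length of the gap**
- T3 is week 18, T4 is week 24, and T5 is 12 months, taken as week 52.
- T3 to T4: 24 − 18 = 6 weeks. T4 to T5: 52 − 24 = 28 weeks.
- Total: 6 + 28 = 34 weeks, and 34/52 = 65.4% of follow-up.
- In those 34 weeks there are 0 SAE checklists, 0 interviews, 0 C-SSRS, 0 NEQ and 2 item 9 assessments.
- Counting only to T4, the gap is 6/24 = 25%.

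**Therapist channel**
- Under Covariates, therapists document SAEs after each session. Side Effects and Adverse Events obliges them to report, and Procedure on (S)AEs sets time limits for doing so.
- Under Intervention, the trial treatment is the first 16 sessions at most, with standard therapy afterwards if still needed. Under Reimbursement, payment for the documentation sheet is tied to completing treatment within the study. The article does not say that documentation continues beyond that.
- A patient who has finished or left therapy has no session in which an SAE could be recorded.

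**Text against schedule**
- Procedure on (S)AEs names interviews alongside questionnaires as the source for follow-up events. Table 3 has no interview after T3.
- The same section ties C-SSRS items to messages at every measurement time. Table 3 and Side Effects and Adverse Events place the C-SSRS at T0 and T3 only.

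**Illustration of scale (assumed risk)**
The article gives no SAE rate. Assume a 12-month risk of 5% (range 2–10%), events spread evenly over the year, and all 900 patients followed.
- 5%: 900 × 0.05 = 45 events; 45 × 0.654 = 29.4 after T3.
- 2%: 18 events; 18 × 0.654 = 11.8 after T3.
- 10%: 90 events; 90 × 0.654 = 58.9 after T3.

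These are events occurring after T3, not events missed. Nothing is subtracted for those that therapists would report.

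**The case against.** The best defence is that T3 is not the only SAE record. Therapists have a named SAE field after each session and a duty to report. The 16 sessions have a maximum number but no stated calendar end, so trial sessions may run past week 18. This stands: for patients still in trial therapy, late SAEs have a structured route. It does not cover those who have finished or left, and it gives no common ascertainment across arms.

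The procedure also does not rest on interviews alone, since questionnaires with item 9 are given at T4 and T5. T3 is only assumed to be post-treatment, so for a patient who finishes early the T3 interview may itself fall in the follow-up period. The mention of interviews therefore need not be a flat contradiction, but it describes nothing that happens after T3. The C-SSRS sentence can fairly be read as applying whenever the scale is given, which makes it loose wording at most.

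Finally, no 12-month safety endpoint is promised, the systematic query coincides with the primary endpoint, and Reimbursement says that T5 onwards is outside the grant. This limits the seriousness of the point. T5 is nevertheless in the planned schedule, and the T4 gap remains in any case.

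A reader might go further and infer that late SAEs will be largely uncounted, that a delayed harm could not show, or that follow-up counts sent to the DSMB will be close to zero by design. The article supports none of these. It gives neither an SAE rate nor the number still in therapy after T3. PHQ-ADS and medication at T4 and T5 can show late worsening, suicidal tendencies and new medication. It describes no separate follow-up count for the DSMB.

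**Conclusion.** The point holds as a gap in ascertainment. From week 18 to month 12, 34 of 52 weeks (65%), no scheduled patient assessment asks about any of the six SAEs. Only item 9 at T4 and T5, and unsolicited or therapist reports, remain. The therapist route is not stated to continue after study treatment, cannot reach patients who have left therapy, and is unblinded.

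The length of the gap follows from the schedule, with 12 months taken as 52 weeks. How many SAEs would be missed, and whether the arms would differ in this, cannot be derived from the article. The 29 events (12 to 59) shown above rest wholly on the assumed risk and even timing. The change is worth making because safety against CBT is a stated aim and the remedy is small. It does not affect the primary analysis.

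**What to change.** - Add the existing SAE checklist, covering the six listed events since the last assessment, to the T4 and T5 online questionnaires, identically in all arms.
- Report SAEs by arm separately for T0–T3 and T3–T5, and state the source of each report (patient query, therapist, other).
- State how long therapist SAE documentation lasts relative to the 16 sessions.
- Reconcile Procedure on (S)AEs with Table 3 on interviews and C-SSRS timing after T3.

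The cost is about six yes/no items in two questionnaires that are already planned, with no new visit, plus some work for study personnel in following up positive answers. The late data would be self-report rather than interview, and a questionnaire cannot capture a completed suicide or reach non-responders.

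Insurer claims, described under Cost Measures as holding "information on costs, diagnoses, and treatments for the following areas: in- and outpatient care, rehabilitation, prescribed medication", could supplement this for events that lead to care. That is possible only if the period covered and the permitted use allow it. The article describes these data for the economic evaluation and states neither.

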IMIs could also be used to optimize the efficiency of psychotherapy. It has been well-established that therapeutic guidance is an active component of IMIs, however, with a yet to be examined ceiling effect from which onward more therapist time does likely not translate into clinically significant higher therapeutic benefits for the average patient (31, 32). Hence, one possible way of implementing blended therapy is to iteratively provide standard psychotherapy combined with Internet- and mobile based self-help modules, with the assumption of non-inferiority. As such, blended therapy could represent a means of providing psychotherapy to more patients in need, against the background of restricted resources as present in most health care systems around the world.

PSYCHOnlineTHERAPY aims to examine the potential of integrated blended therapy by comparing standard CBT-focused outpatient psychotherapy (CBT_standard_) with two implementation variants of integrated blended therapy, (1) PSYCHOnlineTHERAPY_fix_ as a standardized blended therapy concept combining equal numbers of standard therapy sessions and online intervention modules and (2) PSYCHOnlineTHERAPY_flex_, providing therapists with the means of combining standard therapy with online interventions modules as perceived fitting for the respective therapy process at hand. In more detail, the project aims to examine:

the non-inferiority of PSYCHOnlineTHERAPY_fix/flex_ in comparison to CBT_standard_.the cost-effectiveness of PSYCHOnlineTHERAPY_fix/flex_ in comparison to CBT_standard_.the safety of PSYCHOnlineTHERAPY_fix/flex_ in comparison to CBT_standard_.qualitative and quantitative details of the implementation variants with regard to acceptance, feasibility, barriers, and facilitators to identify optimization potential.moderators and mediators of the therapy success as well as potential risks and side effects.

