### Assessments

All assessments will be conducted online (patient and therapist self-reports) or telephone-based (standardized clinical interview SCID-5, HAM-A, QIDS-C). For an overview of instruments at baseline (T0), inter-session assessments at six (T1) and 12 weeks (T2) follow-up, as well as 18 weeks (T3; assumed as post-treatment), 24 weeks (T4) and 12 months post-inclusion follow-up (T5) see Tables 3, 4. PSYCHOnlineTHERAPY might be continued with further follow-up assessments (2–5-year follow-up assessments) in case of patients' informed consent and given follow-up assessment resources.

**Table 3 T3:** Overview of the assessments (patients).

**Variable**	**Instrument**	**Time of measurement**					
		**T0**	**T1**	**T2**	**T3**	**T4**	**T5**

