**Online-questionnaires (self-rated)**							
Depression and anxiety	PHQ-ADS	X	X	X	X	X	X
Quality of Life	AQOL	X			X	X	
Patient satisfaction	ZUF-8				X		
Working alliance	WAI-SR		X		X		
Cost-effectiveness	TIC-P	X			X	X	
Sociodemographics	SR	X	X				
Risk factors	SR	X					
Medication	SR	X			X	X	X
Reasons for dropout	SR				X		
Childhood trauma	CTS	X					
Social support	F-SozU K-6	X			X		
Negative effects	NEQ				X		
Suicidal and self- injurious thoughts and behaviors	C-SSRS	X			X		
Personality functioning	LPFS-BF 2.0	X					
Self-care	SR	X	X	X	X		
Self-management	SMST	X	X	X	X		
Self-efficacy	MHSES	X	X	X	X		
Therapeutic agency	TAI		X	X	X		
Empowerment	SR				X		
CBT-Skills	CBTSQ	X	X	X	X		
Homework implementation	SR		X	X	X		
Loneliness	UCLA	X			X		
Expectations/Credibility	CEQ	X			X		
Attitudes toward blended therapy	APOI	X			X		
Individual therapy goals	FRAPT	X			X		

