#### Primary Outcome

The primary outcome is depression and anxiety severity at post-treatment 18 weeks post-inclusion (T3), assessed with the Patient Health Questionnaire Anxiety and Depression Scale [PHQ-ADS; 16 items, score range: 0–48; (51)]. Depression and anxiety symptoms at all other assessments will be considered as secondary outcomes. PHQ-ADS is the combined sum score of the questionnaires Generalized Anxiety Disorder Screener (GAD-7) and Patient Health Questionnaire (PHQ-9) as a composite measure of depression and anxiety, with good internal consistency [α = 0.88–0.92; (51)].

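### Symptom deterioration is defined on interviews held only at T0 and T3, so transient and post-T3 worsening cannot be classified, although PHQ-ADS is collected at all six assessments

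*Protocol article*

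**What the plan says.** The Introduction lists "the safety of PSYCHOnlineTHERAPY" fix/flex compared with standard CBT among the trial's aims. Under Side Effects and Adverse Events, after the (S)AEs and the Negative Effects Questionnaire (NEQ), the article adds that "depression and anxiety symptom deterioration are determined by means of the QIDS-C and HAM-A". It names no other instrument for deterioration.

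The Assessments section makes these scales "telephone-based (standardized clinical interview SCID-5, HAM-A, QIDS-C". In Table 3 each has two marks, at T0 and T3: "Depression response QIDS X X" and "Anxiety response HAM-A X X". The self-report row has six, T0 to T5: "Depression and anxiety PHQ-ADS X X X X X X".

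PHQ-ADS at T3 is the primary outcome. For the rest, the Primary Outcome section says: "Depression and anxiety symptoms at all other assessments will be considered as secondary outcomes". The Clinical Analyses section applies intention-to-treat to all statistical analyses and multiple imputation to missing data. It does not mention deterioration.

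**The concern.** A trial that replaces some on-site sessions with online modules should be able to show who got worse, and when, in each arm. The deterioration rule looks at one post-baseline moment. It cannot register a patient who worsens at week 6 or 12 and recovers by week 18, or one who first worsens at week 24 or month 12. Imputation cannot repair this, because the two scales are not scheduled at those visits.

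The other systematic harm measures cluster at the same visit. The structured SAE query and the NEQ are at T3, and the modified C-SSRS is at T0 and T3. PHQ-ADS item 9 is read at every assessment but covers suicidality only. Symptom worsening as such is not among the six listed SAEs. (S)AE reports can arise in therapy sessions, but the fix arm has at most 8 standard sessions against at most 16 under standard CBT, so the opportunity to report may differ by arm. PHQ-ADS is scheduled identically in all arms.

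At stake is the completeness of the safety comparison. The non-inferiority test on the primary outcome is not affected.

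**Working it through.** **Step 1: the schedules side by side (Table 3).**

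| Scale | T0 | T1, 6 wk | T2, 12 wk | T3, 18 wk | T4, 24 wk | T5, 12 mo |
|---|---|---|---|---|---|---|
| QIDS-C | X | | | X | | |
| HAM-A | X | | | X | | |
| PHQ-ADS | X | X | X | X | X | X |

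Post-baseline assessments at which deterioration can be observed: 1 of 5 under the stated rule, 5 of 5 with PHQ-ADS. Within the treatment window (T1 to T3) the counts are 1 of 3 and 3 of 3.

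**Step 2: what the rule does with each course.**

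- Worse by week 6 or 12, still worse at week 18, interviewed at T3: classified.
- Worse at week 6 or 12, recovered by week 18: not classifiable.
- First worse at week 24 or month 12: not classifiable.
- No T3 interview: not directly observed. The value is imputed if the general imputation statement covers this endpoint, which the article does not say.

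**Step 3: size of the missed-interview part.** The article gives no figure for deterioration or for T3 interview loss, so there is no plan figure to reproduce. The only plan input is the arm size, 25 clusters × 12 patients = 300. The rest is assumed: share of T3 interviews missing, m = 10% to 30%; true deterioration, p = 5% to 10%; missingness unrelated to deterioration.

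- Expected deteriorated patients per arm = 300 × p: 300 × 0.05 = 15 to 300 × 0.10 = 30.
- Of these, not directly observed = 300 × m × p: 300 × 0.10 × 0.05 = 1.5 to 300 × 0.30 × 0.10 = 9.

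Under these assumptions the unobserved share equals m. It would be larger if worsened patients miss the interview more often, but the article offers nothing from which to estimate that.

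**Step 4: size of the transient and post-T3 parts.** This cannot be calculated from the article. It follows from the schedule that these courses fall outside the definition, whatever their frequency.

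**Step 5: does the secondary PHQ-ADS outcome fill the gap?** Severity at T1, T2, T4 and T5 can be compared between arms. Two arms can share a mean while one contains more patients who worsened, offset by others who improved more. A severity comparison therefore does not supply a deterioration rate.

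**The case against.** The interview choice is defensible. QIDS-C and HAM-A are rated by assessors kept blind to arm, whereas PHQ-ADS is self-reported by patients who know their treatment. T3 is the post-treatment point, so worsening that lasts to a completed T3 interview is captured. A dip at week 6 that resolves is not clearly harm. After the first 16 sessions every arm may continue with standard therapy, so worsening at T4 or T5 is harder to attribute to the arm. Classifying patients at several visits adds false positives. PHQ-ADS has missing data of its own, and T5 compensation is not covered by the grant. Nothing in the article contradicts itself here, and it does not rule out PHQ-ADS analyses. All of this stands. It argues for keeping the interview measure as the main one, but not against a supplementary one.

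A reader might infer two stronger claims. The first is that patients without a T3 interview drop out of the deterioration rate, so that selective loss makes the blended arms look safer. The documents do not support this. Intention-to-treat and multiple imputation are stated for the analyses generally, and the per-protocol analyses restricted to patients with data are additional. Stopping therapy is not the same as leaving assessment: T3 is fixed at 18 weeks from inclusion, its completion is compensated, and reasons for dropout are asked there. The article gives no completion rates by arm.

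The second is that worsening outside T3 goes unseen. It does not. PHQ-ADS severity and item 9 are available at the other assessments, therapists document SAEs after each session, and follow-up events are recorded by study personnel. The NEQ at T3 also looks back over treatment. What is missing is a deterioration rate at those times.

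**Conclusion.** The point holds in a limited form. Deterioration is one of several harm measures, and its definition confines it to one post-baseline assessment out of five. Worsening that resolves before T3 or starts after it cannot be classified. This follows from the article's text and Table 3 and needs no assumption.

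For patients without a T3 interview, the accurate statement is that deterioration is not directly observed and that the article does not say whether imputation reaches this endpoint. The range of 1.5 to 9 unobserved among 15 to 30 expected patients per arm depends wholly on the assumed rates. It shows scale, not bias between arms, and imputation may recover part of it.

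This is a worthwhile strengthening of a stated aim, not an error that undermines the trial.

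**What to change.** Keep blinded QIDS-C/HAM-A deterioration at T3 as the main measure and add, as a supplementary safety analysis by arm:

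- PHQ-ADS reliable deterioration from T0 (reliable change index) at each of T1 to T5, and any such deterioration from T1 to T3.
- For patients without a T3 interview, the last available PHQ-ADS status. The questionnaire is online and separate from the telephone interview, so some of these patients may have a T3 score.
- A statement that imputation covers deterioration, with the T1 and T2 PHQ-ADS scores in the imputation model.

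Fix the reliability value for the index in advance, because it moves the threshold. With the article's internal consistency of 0.88 to 0.92 and the usual 1.96 criterion, the threshold is 1.96 × √(2 × (1 − 0.88)) = 0.96 to 1.96 × √(2 × (1 − 0.92)) = 0.78 baseline standard deviations.

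The cost is a little analysis on scores already held. PHQ-ADS is unblinded self-report, and repeated classification labels some stable patients as worse. The two measures should therefore be shown side by side, with the any-deterioration rate read as a comparison between arms rather than as an absolute frequency of harm.
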